### Participants and recruitment

2.3

We will recruit 384 eligible participants from the Ningxia Yuehai Service Center. The eligible elderly must meet the following inclusion criteria. A CONSORT diagram of participant recruitment is shown in Table 1. We intend to promote the recruitment programme through advertisements on community bulletin boards and community broadcasts. Researchers will register the interested participants for the first time and conduct a corresponding screening assessment. After baseline assessment, eligible participants will be randomly assigned to 1 of the 4 research groups.

**Table 1 T1:**
[figure not shown]
Trial processes chart.

### Inclusion criteria

2.4

Participants must fulfill the following criteria:(i)aged over 60 years;(ii)no long-term regular exercise history, no long-term Tai Chi Chuan or core strength training participation;(iii)no serious movement disorders, such as joint deformity, disease or severe spinal joint pain, severe heart and lung diseases, that would interfere with core strength training and Tai Chi Chuan;(iv)no other serious organic diseases; and(v)voluntary cooperation with the experiment of core strength training.

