## Abstract

**Background::**

According to the national census, China has gradually become an aging society; moreover, aging has become an irreversible worldwide trend in the twenty-first century. Aging can lead to decreased physical function, mobility, cardiopulmonary function and quality of life (QOL). The feasibility and benefits of core strength training (CST) and Tai Chi Chuan (TCC) in older adults (including improving cardiovascular, musculoskeletal, and mental health outcomes) have been confirmed in previous studies. To date, these exercise programmes have not been systematically compared, and the potential benefits of their combined use have not been tested. The primary objective of this **s**tudy protocol is to evaluate the effects of CST compared to those of TCC on the function of the musculoskeletal system and the cardiopulmonary system in older adults.

The second objective is to test the effectiveness of combined physical training that incorporates CST and TCC.

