### Withdrawal criteria

2.6

Participants who meet1 of the following conditions will be withdrawn from the trial:(i)failure to train as required after the experiment;(ii)suffer from bone or joint pain that impacts the continuation of training;(iii)unable to continue training due to other diseases;(iv)assigned to the control group but followed a regular exercise programme.

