### Randomization and allocation concealment

2.7

Following the baseline assessment, the subjects will be randomly assigned to1 of the 4 groups (CG, CST, TCC, and CTG) at a ratio of 1:1:1:1.

The randomization list will be generated through the Statistical Analysis Software (SAS, version 9.1) by a specified research assistant who is not otherwise involved in this study. We will use consecutive numbered, sealing and opaque envelopes to achieve the allocation concealment of the participants. The research manager will inform the eligible participants of the specific allocation results after the baseline assessment is completed.

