### Blinding

2.8

Due to the specificity of the intervention project, it is impossible to implement the blind method for participants and training instructors in this experiment. However, we will specify a designated research assistant to supervise the management of random allocation sequence and to blind coding the allocation by labelling the 4 groups (CG, CST, TCC, and CTG) A, B, C, and D. Furthermore, we will clarify the specific obligations of each investigator: the research assistant and training instructors will not be allowed to participate in the evaluation of outcomes; the outcome assessors and the statistical analysts will not be allowed to participate in screening and allocating. The participants will be told not to mention training forms in front of the assessors. We will uncover the allocation sequence and blind codes after the completion of the statistical analysis.

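### Inclusion criterion (v) asks for cooperation with core strength training only, in a four-arm trial whose main contrast is core strength training versus Tai Chi

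*Protocol article*

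**What the plan says.** All references are to the protocol article.

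- **Section 2.4 (v)**, the only criterion about willingness: "voluntary cooperation with the experiment of core strength training".
- **Section 2.4 (ii) and (iii)** cover both trainings. Criterion (ii) asks for "no long-term Tai Chi Chuan or core strength training participation". Criterion (iii) bars conditions "that would interfere with core strength training and Tai Chi Chuan".
- **Abstract, Background**: the primary objective is "to evaluate the effects of CST compared to those of TCC on the function of the musculoskeletal system" and the cardiopulmonary system. The second objective concerns the combined training.
- **Section 2.7**: "the subjects will be randomly assigned to1 of the 4 groups (CG, CST, TCC, and CTG) at a ratio of 1:1:1:1".
- **Section 2.8**: "it is impossible to implement the blind method for participants and training instructors in this experiment".
- **Section 2.6**: grounds for withdrawal include (i) "failure to train as required after the experiment" and (iv) a control participant taking up regular exercise.
- **Section 2.13**: intention-to-treat and per-protocol analyses are both planned, with missing values filled by last observation carried forward (LOCF).
- **Section 2.15**: written consent follows full information about the study.

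**The concern.** A criterion on willingness should ask whether a person will accept whatever the randomisation gives. This one asks about one of the two trainings being compared. Two of the four arms contain Tai Chi and one involves no training, so for three arms the criterion leaves all or part of the allocation unscreened.

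If some enrolled people accept CST but not Tai Chi, those allocated to TCC or to the combined group may not train. If some came in order to train, those allocated to control may start exercising. Both are grounds for withdrawal under Section 2.6. Withdrawal that differs by arm would matter most for CST versus TCC, the main contrast, and for the comparisons involving the combined group.

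**Working it through.** No figure in the document tests this point, so the check is mainly a comparison of texts.

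**1. Who passes criterion (v), read literally**

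| Volunteer accepts | Passes (v)? | Arms the volunteer would follow |
|---|---|---|
| CST, TCC and control | yes | all four |
| CST and control, not TCC | yes | CST, control |
| CST only | yes | CST |
| TCC and control, not CST | no | TCC, control |

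Everyone who passes accepts CST. Acceptance of the other allocations is not screened.

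**2. Whether another entry rule closes the gap.** Exclusion (i) in Section 2.5 concerns inability to train over the 12 weeks, not unwillingness, and is neutral between the trainings. Consent (Section 2.15) covers the whole study, but is not stated as agreement to accept any allocation. The gap is narrowed, not closed.

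**3. Whether the arms differ at baseline.** They do not on this account. Eligibility is settled before randomisation and is the same for all arms, so the share of people unwilling to do Tai Chi is balanced in expectation. Any difference can only arise afterwards, when the same attitude meets different allocations.

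**4. The route after randomisation**

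- Participants know their allocation (Sections 2.7 and 2.8).
- A refuser in the TCC or combined group meets 2.6(i), taking that item to mean failure to train during the trial.
- Controls have no training to fail; their route is 2.6(iv).
- A person withdrawn without an end-of-intervention measurement has the baseline value carried forward, which is a change of zero. The same person leaves the per-protocol set.

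**5. Illustration for CST versus TCC.** The refusal share r is an assumption; the document gives none. Take r from 0 to 10% in the TCC arm and none in the CST arm. Planning values for lumbar spine BMD change (Section 2.2) are CST 0.043 and TCC 0.021, a difference of 0.022, with 96 per arm. Assume also that refusers would otherwise have had the average TCC change, and that none is measured again.

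- People affected = 96 × r
- TCC mean after LOCF = 0.021 × (1 − r)
- Apparent difference = 0.043 − that mean

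| r | People | TCC mean | Difference | Relative to 0.022 |
|---|---|---|---|---|
| 0% | 0 | 0.0210 | 0.0220 | none |
| 5% | 4.8 | 0.01995 | 0.02305 | +4.8% |
| 10% | 9.6 | 0.0189 | 0.0241 | +9.5% |

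**6. Power.** The pooled SD is √[(0.108² + 0.0915²)/2] = 0.100. With 96 randomised per arm, normal-approximation power for a difference of 0.022 (two-sided 5%) is 27.5% with 20% dropout in each arm (76.8 and 76.8 retained). It is 27.1% with 10% dropout in CST and 30% in TCC (86.4 and 67.2). These dropout splits are assumed; Section 2.2 gives one overall rate of 20%. Unequal dropout of this size hardly moves power, so any harm would be bias.

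**The case against.** The strongest reply is that criterion (v) is just a loose name for this trial. Its neighbours cover both trainings, and participants consent to a study with four groups, so a person unwilling to risk Tai Chi or control can decline then. This is plausible and lowers the practical risk. It does not rescue the text: on that reading an operative eligibility rule misnames the trial, and screeners could apply it differently.

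A second reply is that the plan already limits the damage. An intention-to-treat analysis is specified, and Section 2.14 says staff will try to obtain a last evaluation before someone leaves. Where that succeeds, there is a measured value instead of a carried-forward baseline. This also stands in part: it does nothing for the per-protocol analysis, and it depends on people agreeing to return.

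A reader might go further and infer that the trial selects people who favour CST. The document does not support that. Agreeing to cooperate is acceptance, not preference, and nothing is said about preference in any arm. Nor does the wording show that screening on CST alone was a deliberate design decision.

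**Conclusion.** The point holds as a wording defect in an eligibility rule, of low severity. Criterion (v) does not fit criteria (ii) and (iii), the four-arm randomisation or the primary contrast. With open allocation, the withdrawal rules, LOCF and a per-protocol analysis, it could allow unequal adherence or withdrawal in the arms containing TCC (TCC and combined) and in the control arm.

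The size cannot be computed from the document. The illustration, a shift of 0 to about 10% in the CST–TCC difference in favour of CST, rests wholly on an assumed refusal share, on a literal reading of (v) and on no last evaluation being obtained. It shows a possible direction and is not an estimate.

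Three stronger conclusions might be drawn and should not be: that the groups differ at baseline (they do not on this account), that withdrawals will concentrate outside the CST arm (no arm-specific rate is given), and that the trial loses material power this way (step 6 shows little loss).

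**What to change.** Replace criterion (v) with: willing to be assigned to any of the four groups and to follow the assigned programme for 12 weeks. For controls, the assigned programme means keeping to their usual lifestyle, as Section 2.9.1 already describes.

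The change is one line in the criteria and the same line on the screening form. Sample size, randomisation and analysis are untouched. The small downside is that a few volunteers with a strong preference for one training, or unwilling to be controls, are screened out.

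If recruitment has already begun under the present wording, the sponsor should state how screeners applied it and report reasons for withdrawal by arm, so that readers can judge whether refusal of the allocation differed between groups.

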### Exclusion criteria

2.5

Participants who meet1 of the following conditions will be considered ineligible:(i) inability to train for an extended period time (this experiment requires 12 weeks); (ii) cognitive impairment;(iii) severe mental illness; or(iv) other active interventions that may affect the outcome of this study.

### Withdrawal criteria

2.6

Participants who meet1 of the following conditions will be withdrawn from the trial:(i)failure to train as required after the experiment;(ii)suffer from bone or joint pain that impacts the continuation of training;(iii)unable to continue training due to other diseases;(iv)assigned to the control group but followed a regular exercise programme.

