#### Control group

2.9.1

The subjects in the control group will maintain their original lifestyle and perform routine activities of daily living. During the intervention period of 12 weeks, if the participants change their daily activities or increase their amount of exercise or exercise intensity, they will be required to record the details of the extra physical activity, including the type, intensity, and activity time.

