### Statistical analysis

2.13

We will use the intention-to-treat (ITT) analysis and per-protocol subject (PPS) analysis to analyze the primary and secondary outcomes. When there is a missing data, we will use the last observation carried forward method to deal with it. The continuous variables will be expressed as the mean ± SD. All categorical variables will be expressed in terms of their standard error. After examining whether the data accord with normality test (the Kolmogorov–Smirnov test), we will use ANOVA (assuming a normal distribution) or Kruskal–Wallis (a nonparametric test) to analyze the measurement results. We will use the Bonferroni method to appropriately adjust the overall level of significance for multiple outcomes.

For all the analyses of this study a significance level of 95% (two-sided *P* < .05) will be used. All statistical tests will be conducted using SPSS Statistical Software (IBM SPSS Statistics for Windows, Version 21.0. Armonk, NY).

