### Quality control

2.14

To ensure that this trial can be completed with high quality, the researcher must strictly adhere to the requirements of the trial protocol, and the participants must be strictly in accordance with the inclusion and exclusion criteria. In addition, to ensure the authenticity and credibility of the data, we will advise participants that they are free to withdraw from the study at any stage for any reason without any consequences. Of course, if possible, we will try our best to persuade the participants to undergo the last evaluation before their withdraw. Thus, we can do an intention-to-treat (ITT) analysis. The participants must be grouped according to the random allocation sequence produced by the statistical software SAS 9.1. We stipulate that assessors and statistical analysts will not participate in the recruitment and allocation of participants.

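### Section 2.6 withdraws people from the trial, not only from training, for what they do after randomisation, which undermines the planned ITT analysis with avoidable, informative missing outcomes

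*Protocol article*

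**What the plan says.** Section 2.6 (Withdrawal criteria) states that participants who meet one "of the following conditions will be withdrawn from the trial". Criterion (i) is "failure to train as required after the experiment"; the timing is loosely worded, but it can only refer to conduct after allocation. Criteria (ii) and (iii) cover bone or joint pain, or other disease, that prevents further training. Criterion (iv) is "assigned to the control group but followed a regular exercise programme".

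Section 2.13 (Statistical analysis) states: "We will use the intention-to-treat (ITT) analysis and per-protocol subject (PPS) analysis to analyze the primary and secondary outcomes". For missing data, "we will use the last observation carried forward method to deal with it".

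Section 2.14 (Quality control), after saying that participants may leave freely, adds that "if possible, we will try our best to persuade the participants to undergo the last evaluation before their withdraw", and gives this as what makes an ITT analysis possible.

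Section 2.9.1 (Control group) says of controls who change their activities or exercise more that "they will be required to record the details of the extra physical activity, including the type, intensity, and activity time". It does not say whether they stay in the trial.

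Section 2.7 places randomisation straight after baseline, so every criterion in 2.6 operates after allocation.

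**The concern.** An ITT analysis compares the arms as randomised, so it needs outcomes from non-adherers, from people who had to stop, and from controls who took up exercise. Section 2.6 ends participation for exactly these people. The selection also runs in opposite directions: the training arms lose those who train least or cannot go on, and the control arm loses those who exercise most. If exercise behaviour is related to BMD change, the people still measured at the end of the intervention (week 13 in section 2.1, 12 weeks in 2.11 and 2.12.5) and at week 25 are no longer comparable across arms.

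The protocol itself creates this data loss. An analysis plan cannot recover measurements that the protocol stopped collecting.

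**Working it through.** **No stated figure to reproduce.** The documents give no rate of non-adherence or contamination. The nearest figure is the combined 20% dropout and exit rate in section 2.2, which enters as 80 × 1.2 = 96 per arm; 20% of 96 is about 19 people per arm.

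**Inputs from section 2.2**
- Mean BMD change: CG 0.007, CST 0.043, TCC 0.021, CTG 0.051.
- Differences from control: TCC 0.014, CST 0.036, CTG 0.044. CST − TCC = 0.022.
- Pooled SD = √[(0.098² + 0.108² + 0.0915² + 0.099²)/4] = √0.00986 = 0.0993.

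**Assumptions (not in the documents)**
- The whole 20% is selected on behaviour: the least adherent in a training arm, the most active among controls.
- Behaviour and BMD change are jointly normal with correlation r = 0.1 to 0.3.
- Withdrawal comes before the end-of-intervention visit. Under LOCF with no exit evaluation, baseline is carried forward, i.e. zero change.

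**Step 1: no true effect.** Removing a 20% tail shifts the mean of those remaining by r × [φ(z₀.₂₀)/0.80] × SD = r × (0.280/0.80) × 0.0993 = r × 0.0348. The shift is upwards in a training arm and downwards in control, so the spurious difference is twice this. With zero change imputed for the 20%, it is multiplied by 0.8.

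| r | Shift per arm | Training − control, those remaining | Training − control, LOCF | Two-sided type I error, one pairwise test |
|---|---|---|---|---|
| 0.1 | 0.0035 | 0.007 | 0.006 | 0.07 |
| 0.2 | 0.0070 | 0.014 | 0.011 | 0.14 |
| 0.3 | 0.0104 | 0.021 | 0.017 | 0.26 |

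The error rate is nearly the same for both analyses. The zeros shrink the difference by 0.8, but they also reduce the variance to about 0.8 SD² over 96 people. Both standardised shifts are therefore about 2 × r × 0.35 × √(96 × 0.8/2), which is 0.43 at r = 0.1.

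If only 10% per arm were withdrawn in this way, the difference among those remaining would be 0.004 to 0.012.

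**Step 2: the planned effects are true.** With LOCF zeros, the expected difference is 0.8 × (planned difference + 2 × shift).

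| Contrast | Planned | r = 0.1 | r = 0.2 | r = 0.3 |
|---|---|---|---|---|
| TCC − CG | 0.014 | 0.017 | 0.022 | 0.028 |
| CST − CG | 0.036 | 0.034 | 0.040 | 0.045 |
| CTG − CG | 0.044 | 0.041 | 0.046 | 0.052 |

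The result may lie above or below the planned value, depending on the contrast and on r.

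**Step 3: CST against TCC.** Criteria (i) to (iii) apply alike to both arms. With equal withdrawal and equal r the shifts cancel, and only LOCF attenuation remains: 0.8 × 0.022 = 0.018.

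**The case against.** The strongest reply is that the plan does keep withdrawn people in the ITT set: section 2.14 seeks a last evaluation for that very purpose, and section 2.13 fills gaps by LOCF. This stands in part. A reader might infer that 2.6 flatly contradicts the ITT analysis, and the documents do not support that. But the evaluation is sought only where possible, in a sentence that follows one on voluntary withdrawal, and it precedes exit. It supplies neither scheduled outcome after a withdrawal that the protocol imposes. Membership of the ITT set is kept; most of its content is not.

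Three other stronger readings also go too far.
- *The bias favours training.* This holds in the no-effect illustration. If training works, the carried-forward zeros pull the other way, as step 2 shows.
- *The comparison of CST with TCC is distorted by selection.* That needs withdrawal or selection to differ between the two arms, and the documents do not say that it would.
- *Section 2.9.1 contradicts criterion (iv).* Section 2.9.1 only requires a record of extra activity, and that record could be how criterion (iv) is detected. What is missing is the point at which recorded activity becomes a regular programme.

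It is also fair to say that the 20% covers all causes of loss, so assigning all of it to behaviour is a worst case.

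**Conclusion.** The point holds as an undermining of the ITT analysis. Section 2.6 turns non-adherence, inability to continue and contamination into avoidable, informative missing outcomes, by rules that differ between the training arms and control. Under the stated worst-case withdrawal rate, and with r of 0.1 to 0.3, the spurious training-minus-control difference would be comparable with the smaller planned effect: at r = 0.2 it is 0.014 among those remaining, equal to the whole planned TCC − CG difference. The correlation, and the share of the 20% that is due to behaviour, are assumptions. The mechanism follows from the text; the size and net direction of the bias cannot be fixed from it. The change is needed because the lost measurements cannot be recovered once follow-up ends.

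**What to change.** - Reword section 2.6 so that criteria (i) to (iv) do not end outcome assessment. Leave the rules on stopping training as they are.
- Invite every randomised participant to the scheduled week-13 and week-25 assessments unless consent is withdrawn.
- Analyse ITT as allocated, using these data, so that LOCF is not needed for people who merely stopped or changed activity.
- Use adherence and contamination, criteria (i) and (iv), only to define the per-protocol set.
- Reconcile 2.6(iv) with 2.9.1 by stating when recorded extra activity counts as a regular exercise programme.

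The cost is a short amendment and a modest number of extra assessments at visits that already exist: at most about 19 people per arm if the whole 20% allowance were of this kind.

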### Randomization and allocation concealment

2.7

Following the baseline assessment, the subjects will be randomly assigned to1 of the 4 groups (CG, CST, TCC, and CTG) at a ratio of 1:1:1:1.

The randomization list will be generated through the Statistical Analysis Software (SAS, version 9.1) by a specified research assistant who is not otherwise involved in this study. We will use consecutive numbered, sealing and opaque envelopes to achieve the allocation concealment of the participants. The research manager will inform the eligible participants of the specific allocation results after the baseline assessment is completed.

### Blinding

2.8

Due to the specificity of the intervention project, it is impossible to implement the blind method for participants and training instructors in this experiment. However, we will specify a designated research assistant to supervise the management of random allocation sequence and to blind coding the allocation by labelling the 4 groups (CG, CST, TCC, and CTG) A, B, C, and D. Furthermore, we will clarify the specific obligations of each investigator: the research assistant and training instructors will not be allowed to participate in the evaluation of outcomes; the outcome assessors and the statistical analysts will not be allowed to participate in screening and allocating. The participants will be told not to mention training forms in front of the assessors. We will uncover the allocation sequence and blind codes after the completion of the statistical analysis.

